#### Design

A cross-sectional factorial survey experiment will be conducted to investigate the decision-making process of health care professionals concerning potential LVC practices. This approach combines survey research with experimental research [21, 25]. Here, the professionals are asked to make multiple decisions based on random generation of the vignettes (i.e., concrete, fictive clinical case descriptions [21]). An FSE allows analyses of professionals’ judgments and is particularly suitable for investigating complex situations with multiple stimuli. This approach has the unique ability to simultaneously measure the independent effects of respondents and situational factors without the need to give participants every possible combination of variables. This method is widely used to study health care professionals’ decision-making, e.g., [26–29]. FSE is a suitable method to study the often, and somewhat, sensitive issue of LVC because it provides a less personal and therefore less threatening way of exploring the topic [21]. Furthermore, professionals’ decision-making is often challenging to study with conventional social science methods such as interviews and observations [21]. Although the decisions made in an FSE are hypothetical and do not replicate real life, it is considered suitable for providing an in-depth insight into decision-making processes, which this project aims to do. Apart from manipulating the factors in the vignettes, we will collect relevant data about health care professionals, which may affect how they make their decisions. Following the previous literature [14, 30], we will consider their length of clinical experience, fear of possible litigation, and a tendency to worry that they may miss a certain diagnosis. For the sensitivity analysis, we will control gender.

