**Fig. 1 Fig1:**
[figure not shown]
Randomly populated vignette example

Following the recommendations for FSEs, we will use approximately 7 ± 2 dimensions with 2–3 levels for each of these [21, 25]. In this way, we will be able to empirically test how differences in the dimensions impact the participants’ decisions (e.g., a low-value practice is strongly OR not at all required by a patient, low OR medium OR high costs are related to providing it, and the evidence is clear OR unclear for the lack of clinical benefits). Judging several similar, but not identical, situations by each respondent allows the FSE to decompose the structure of the individuals’ answer behaviors and thereby uncover the impact of the different factors [21]. The dependent variable will be the respondent’s decision to provide the practice described in the vignette, using a visual analog scale from 0% (extremely unlikely) to 100 % (extremely likely).

The vignette universe will be generated by crossing all of the possible combinations (Cartesian product) of the vignette dimensions’ categories to ensure orthogonality across the factors [21]. The experimental design (i.e., vignette universe) will be divided into different decks (blocks) presented to different respondents. This way, we will be able to use a larger overall number of vignettes to enhance statistical efficiency [21]. For blocking to decks, we will use deliberate blocking techniques based on design efficiency (D-efficiency) [21]. A minimum of five respondents will assess each deck [21]. We will use the SAS macro “%mktblock” to ensure a randomized distribution of the whole vignette universe over the decks in order to attain maximum statistical efficiency. By distributing the different questionnaires as evenly as possible, we will ensure that the correlations between dimensions are close to 0 and not significant.

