#### Participants and procedure

First, managers for each primary care center will be approached to anchor the project and to obtain approval for the professionals’ participation. Based on our previous experiences conducting surveys with an organization, we estimate that at least 60% of the centers will participate (i.e., at least 42 centers). The number of professionals at each center varies, commonly from 15 to 20. This estimate would give us a population of professionals that is large enough for the planned survey (at least 630–840 individuals, estimated response rate 60%) [21], although a more thorough power calculation will be performed when the vignettes have been finalized, i.e., the number of factors and dimensions is determined. SAS software will be used for the power analysis. We plan to use quota sampling as our sampling technique and multiple regression analyses for the data analysis. Although simple randomization is common, the current FSE literature proposes that quota sampling has advantages in understanding confounded parameters. We will, therefore, based on the results of the literature review, investigate whether a specific characteristic in the respondent population (e.g., gender) can be an appropriate factor for stratification in a quota sampling. Otherwise, we will use random sampling and carefully target the potential limitations of this method.

Each survey respondent will answer 9–12 vignettes. This number was determined based on prior research showing that health care professionals are able to provide reliable answers to this number of vignettes [21, 26, 29]. The number of vignettes will be based on the time the participant are estimated to be able to spend on the survey (max. 15 minutes), the difficulty and complexity of the vignettes and statistical considerations (e.g., power) [21].

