#### Statistical analysis

Because each respondent will evaluate multiple vignettes, this implies a hierarchical data structure in which the responses (decisions to provide the LVC practice in each scenario) are nested within respondents (healthcare professionals). To address this violation of the classical regression assumption of uncorrelated error terms, mixed-effects models will be performed with vignettes’ dimensions as level 1 and respondents as level 2. First, a random intercept-only model with no predictors (i.e., null model) will be performed to calculate an intraclass correlation coefficient (ICC) and to benchmark model fit. Then, vignette dimension variables and respondent variables, as well as their interactions, will be added sequentially. In the case of low ICC coefficients, regular multivariable regressions will be performed alongside multilevel analyses for a sensitivity test.

### Study 2

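### The ordinary-regression sensitivity test, run only when the null-model ICC is low, gives standard errors that are too small for respondent variables; the main mixed model is not affected

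*Protocol article*

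**What the plan says.** Under Methods, Study 1, Statistical analysis, the protocol article recognises that ratings are nested within respondents. It gives its reason for the model as "To address this violation of the classical regression assumption of uncorrelated error terms" and states that "mixed-effects models will be performed with vignettes’ dimensions as level 1 and respondents as level 2". The ICC is taken from a first model that has a random intercept and no predictors. Vignette dimensions, respondent variables and their interactions are added afterwards. The section then says: "In the case of low ICC coefficients, regular multivariable regressions will be performed alongside multilevel analyses for a sensitivity test".

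Under Study 1, Participants and procedure, directly after the sentence on software for the power analysis, the article says: "We plan to use quota sampling as our sampling technique and multiple regression analyses for the data analysis". No multilevel qualifier is attached. The same section gives the cluster size: "Each survey respondent will answer 9–12 vignettes".

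Two kinds of predictor enter the models. Respondent variables are listed under Design: "we will consider their length of clinical experience, fear of possible litigation, and a tendency to worry that they may miss a certain diagnosis". The manipulated factors are described under Study materials: "we will use approximately 7 ± 2 dimensions with 2–3 levels for each of these". The first research question covers both, since it includes professionals' individual characteristics among the determinants to be weighed.

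**The concern.** The article says that nesting breaks an assumption of ordinary regression, then uses ordinary regression as a check when the ICC looks small. What matters for a respondent variable is the ICC multiplied by the number of ratings per person less one, not the ICC alone. With 9–12 ratings, an ICC that many would call low still inflates the variance appreciably. Disagreement between the check and the mixed model on a respondent variable could then come from the known error in the check, and apparent support from the check would be too generous.

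The trigger adds a second weakness. The ICC that governs the standard errors is the one left after the vignette dimensions are in the model. The null-model ICC is a different quantity, and usually a smaller one in a design that deliberately creates variance within respondents.

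Finally, the phrase in the sampling paragraph does not match the statistical section, and the power calculation beside it has still to be done.

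**Working it through.** **The plan's own figure.** 42 centres × 15 = 630 and 42 × 20 = 840 professionals, as stated. At the stated 60% response this gives 0.60 × 630 = 378 to 0.60 × 840 = 504 respondents, hence 378 × 9 = 3,402 to 504 × 12 = 6,048 ratings. The article states no ICC, so the ICC values below are assumptions shown as a range.

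**Respondent variables.** With m ratings per respondent, the design effect is DEFF = 1 + (m − 1) × ICC. The true standard error is √DEFF times the conventional one, and a nominal 5% test has actual level 2 × [1 − Φ(1.96/√DEFF)]. The ICC here is the one conditional on the predictors in the model. Example: m = 12 and ICC = 0.05 give DEFF = 1 + 11 × 0.05 = 1.55, √1.55 = 1.245, 1.96/1.245 = 1.574, and an actual level of 11.5%.

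**Vignette dimensions.** For a factor balanced within respondents, with a random intercept only, the conventional standard error is 1/√(1 − ICC) times the true one.

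| Assumed ICC | DEFF, m = 9 to 12 | True/conventional SE, respondent variable | Actual level of 5% test, respondent variable | Conventional/true SE, vignette dimension |
|---|---|---|---|---|
| 0.01 | 1.08–1.11 | 1.04–1.05 | 5.9–6.3% | 1.005 |
| 0.02 | 1.16–1.22 | 1.08–1.10 | 6.9–7.6% | 1.010 |
| 0.05 | 1.40–1.55 | 1.18–1.25 | 9.8–11.5% | 1.026 |
| 0.10 | 1.80–2.10 | 1.34–1.45 | 14.4–17.6% | 1.054 |

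**Check by simulation** (378 respondents, seven two-level dimensions, 1,000 runs per setting). For a respondent variable, the actual level was 9.8% at m = 9 and 11.4% at m = 12 with ICC 0.05, and 17–19% at m = 12 with ICC 0.10. For a vignette dimension it was 4.2–5.8%. If respondents differ in how they weigh a dimension (assumed slope SD 0.3–0.4, with intercept plus residual variance set to 1), the direction reverses: the true standard error exceeds the conventional one by 6–15%, and the level was 5–9%.

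**The trigger.** Write τ² for respondent variance, σ²ₑ for residual variance and σ²ᵥ for variance due to the vignette dimensions. The conditional ICC is τ²/(τ² + σ²ₑ). The null-model ICC is approximately τ²/(τ² + σ²ₑ + σ²ᵥ). Let R² be the share of within-respondent variance that the dimensions explain (assumed). Setting τ² + σ²ₑ = 1, a conditional ICC of 0.10 with R² = 20% gives σ²ᵥ = 0.90 × 0.20/0.80 = 0.225, and a null ICC of 0.10/1.225 = 0.082.

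| Conditional ICC | Null ICC, R² = 20% | Null ICC, R² = 40% |
|---|---|---|
| 0.05 | 0.040 | 0.031 |
| 0.10 | 0.082 | 0.062 |
| 0.20 | 0.167 | 0.130 |

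Simulated means were close: 0.039 and 0.028, 0.080 and 0.058, 0.165 and 0.128. If decks are balanced so that their mean vignette effects are equal, the estimated τ² falls by a further σ²ᵥ/(m − 1). A conditional ICC of 0.05 with R² = 20% then appears as 0.016 (m = 9) to 0.023 (m = 12).

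**The case against.** The strongest reply is that this concerns an optional secondary analysis. A reader might infer that ordinary regression takes over when the ICC is low. The article does not say so: the check runs beside the multilevel analyses, and the main inference comes from the mixed model at any ICC. This stands, and it limits the point.

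It is also fair that the manipulated dimensions are barely affected. Under a random intercept the error is small and conservative, and coefficients can be compared between models whatever their standard errors. This stands too, with the caveat that varying slopes reverse the direction.

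On the trigger, the null-model ICC is a legitimate quantity. It is low only relative to the ICC conditional on the dimensions. Respondent variables entered later reduce the between-respondent variance and can offset the gap, and its size depends on an R² that the article does not give. A low value also only makes an extra analysis more likely. So the trigger is weak, but it does not damage the main results.

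A reader might also infer that the power calculation will treat every rating as independent. Nothing shows this. The phrase describes data analysis, the power calculation is deferred until the vignettes are final, and multiple regression can loosely include multilevel models. Only the mismatch in wording stands.

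The article does not state which standard errors the check uses, nor a cut-off for a low ICC. Both may be settled elsewhere and are not counted here as omissions. But regular regression, set against multilevel analysis, reads most naturally as regression with conventional standard errors.

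**Conclusion.** The point holds for the sensitivity test only. The mixed-effects model is an appropriate main analysis. The added ordinary regression, with conventional standard errors, would be anti-conservative for respondent variables even where the ICC is low: roughly double the nominal error rate at ICC 0.05, and about three times at 0.10. For vignette dimensions it would be nearly right if only intercepts vary. Making the check depend on a null-model ICC gives false reassurance, since the residual clustering will tend to be larger than the value that triggered it.

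These sizes rest on assumed ICC and R² values, on 9–12 ratings per respondent, and on conventional standard errors in the check. The unqualified reference to multiple regression is an inconsistency to reconcile, not evidence of a wrong power calculation. Overall the point is minor to moderate.

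**What to change.** In Statistical analysis, remove the condition on a low ICC. Then either delete the ordinary regression, or run it whatever the ICC with standard errors clustered on respondent. With several hundred respondents, clustering should bring the level for respondent variables back close to 5%. If an ICC is to be reported as a measure of clustering, also give it from the model that contains the vignette dimensions.

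In Study 1, Participants and procedure, replace the reference to multiple regression with the mixed-effects model, so that the pending power calculation is based on the model that will be fitted.

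The cost is two sentences and one software option. The downside is that standard errors for respondent variables in the check, and possibly the calculated power for them, will look less favourable.

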#### Participants and procedure

The knowledge gained about how professionals make decisions when dealing with LVC practices will be utilized for creating practical suggestions that can be valuable for key actors involved in health care organizations and steering the de-implementation of LVC. Specifically, we will develop a conceptual framework for professionals’ decision-making concerning de-implementation based on the results from the FSE (Study 1), relevant literature reviews [14, 22] and group interviews, and a theoretical approach (i.e., theory of street-level bureaucracy). These sources will be used to gradually shift from an intensive focus on how de-implementation decisions are made to the potential solutions to improve the process. It will be iteratively tested and further developed with the professionals, the local R&D partner, and other researchers in scientific conferences in order to obtain both optimal scientific rigor and practical usefulness.

Based on this framework, intervention suggestions (e.g., checklists and decision support tools) for facilitating professionals’ decision-making concerning the de-implementation of low-value practices will be developed. Suggestions will be relevant for all levels in the health care system (e.g., national, regional, and organizational) and will focus on facilitating professionals’ decision to engage in de-implementation. The intervention suggestions will be developed in workshops with professionals and other stakeholders involved in organizations for de-implementing LVC.

The conceptual framework will be presented to guide participants’ efforts to propose suitable interventions. We will use an interactive, 2-step process [32] in which participants are first asked to brainstorm potential interventions by answering a specific question (e.g., What can facilitate professionals’ decision-making about the provision of LVC?). Thereafter, these suggestions are rated by the participants for their potential impact, feasibility as well as strengths and weaknesses in health care. Based on previous experience with this method [33], approximately 3–6 workshops will be conducted.

## Discussion

This project aims to contribute to knowledge and practice concerning de-implementation of LVC practices by focusing on the decision-making processes among health care professionals. More specifically, the study will provide three main contributions to the topic. First, the project’s novel contribution lies in approaching the well-known research-to-practice gap by investigating how decisions about abandoning the LVC practices are made rather than by studying which practices need to be abandoned. Thus, the project targets one of the main knowledge gaps related to de-implementation: understanding health care professionals’ perspective and their judgments for solving potential tensions related to the provision of LVC practices. A survey among physicians demonstrated that a majority of them feel that a great deal of responsibility falls on them to make sure their patients avoid unnecessary tests or procedures; these physicians also believed that they are in the best position to address the problem [11]. By taking this perspective, this project will contribute to research and practice by investigating how healthcare professionals make their decisions to prescribe or to avoid a LVC test or procedure. Specifically, we will provide understanding on the decision-making processes by observing how healthcare professionals balance factors identified as determinants for the use of LVC [14]. By juxtaposing and combining these factors, we may be able to identify which of them plays a more deciding role in their judgments, but also which combinations of factors lead to a more frequent decision not to utilize a practice considered as low value.

Second, the project will develop a conceptual framework for professionals’ decision-making about LVC practices. This can be used as a framework in future studies that aim to answer which factors are relevant for health care professionals’ decisions regarding a specific LVC practice. We have an opportunity to compare the proposed framework with existing frameworks for implementation (i.e., putting new practices in place) as it is possible that the decision-making processes differ when something new is implemented as compared to when something is de-implemented. Likely, there will be some overlap between implementation and de-implementation with regard to the determinants, but their relative importance may differ between implementation and de-implementation [22]. Thus, this step will highlight potential differences in these two processes and contribute to specifying the distinctiveness of the de-implementation as a separate research and practice area [34].

Third, evidence-based intervention suggestions will be developed to offer practical solutions to health care professionals and managers. These interventions will aim at facilitating professionals’ decision-making concerning the de-implementation of low-value practices. The suggestions can be suitable for all levels in the health care system (e.g., national, regional, and organizational) depending on their potential impact on facilitating professionals’ de-implementation decision-making. Because decision-making about de-implementation is an under-researched area, not many solutions are available to facilitate this process for health care professionals. This project will offer the research community the opportunity to evaluate the impact of these solutions on de-implementation processes in future studies. These suggestions can later be evaluated for their impact in different clinical settings. These workshops are also an important step in disseminating the findings and providing knowledge on de-implementation to health care stakeholders. Effective interventions for decreasing the use of ineffective practices in health care will lead to improved quality of care provided in the future.

## Data Availability

The datasets used will be available from the corresponding author on reasonable request.

## Abbreviations

LVC: Low-value care
FSE: Factorial survey experiment
